## 2. OBJECTIVE(S) AND ENDPOINT(S)

| Objectives                                                                                                                                                                                                                                                                                                                                                                                               | Endpoints                                                                                                                                                                                                                                                                                                                                                                                                                                                                                                                                                                                                                                                                                                                                                                                                |
|----------------------------------------------------------------------------------------------------------------------------------------------------------------------------------------------------------------------------------------------------------------------------------------------------------------------------------------------------------------------------------------------------------|----------------------------------------------------------------------------------------------------------------------------------------------------------------------------------------------------------------------------------------------------------------------------------------------------------------------------------------------------------------------------------------------------------------------------------------------------------------------------------------------------------------------------------------------------------------------------------------------------------------------------------------------------------------------------------------------------------------------------------------------------------------------------------------------------------|
| Primary                                                                                                                                                                                                                                                                                                                                                                                           |                                                                                                                                                                                                                                                                                                                                                                                                                                                                                                                                                                                                                                                                                                                                                                                                          |
| 
 
1. To assess the safety and tolerability of single and repeat oral dose of 160 mg EC darapladib in healthy Chinese Subjects.
 
2. To assess the primary PK parameters of single and repeat oral dose of 160 mg EC darapladib in healthy Chinese Subjects.
 
                                                                                       | 
 
1. Clinical safety data from spontaneous AE reporting, 12-lead electrocardiogram (ECG) recording, vital sign measurement, nursing/physician observation and clinical laboratory examination will be summarized and any clinically significant abnormalities described.
 
2. The primary PK endpoints of interest are area under the concentration-time curve from time zero (pre-dose) to last time of quantifiable concentration (AUC[0-t]), area under the concentration-time curve from time zero (pre-dose) extrapolated to infinite time (AUC [0-∞]), maximum observed concentration (Cmax) and accumulation ratios (Cmax accumulation ratio [Rcmax] and observed accumulation ratio [Ro]) of darapladib.
 
 |
| Secondary                                                                                                                                                                                                                                                                                                                                                                                         |                                                                                                                                                                                                                                                                                                                                                                                                                                                                                                                                                                                                                                                                                                                                                                                                          |
| 
 
1. To assess the secondary PK parameters of single and repeat oral dose of 160 mg EC darapladib and the PK parameters of the pharmacologically active metabolite SB-553253 in healthy Chinese Subjects.
 
2. To evaluate the inhibition of plasma Lp-PLA2 activity after repeat oral doses of 160 mg EC darapladib in healthy Chinese Subjects.
 
 | 
 
1. The secondary PK endpoints of interest are time of occurrence of Cmax (Tmax) and terminal phase half-life (T1/2) of darapladib and AUC(0-t), AUC(0-∞), Cmax, T1/2 and Tmax of the pharmacologically active metabolite SB-553253 (as data permit).
 
2. Plasma Lp-PLA2 activity, expressed in terms of percent inhibition relative to baseline.
 
                                                                                                                                                                                                                                                                                                                             |
| Exploratory                                                                                                                                                                                                                                                                                                                                                                                       |                                                                                                                                                                                                                                                                                                                                                                                                                                                                                                                                                                                                                                                                                                                                                                                                          |
| To describe the plasma concentration-Lp-PLA 2 activity inhibition relationship following repeat oral doses of 160 mg EC darapladib.                                                                                                                                                                                                                                                           | Estimation of PK/PD parameters [such as half maximum inhibitory concentration (IC 50 ), Zero effect dose (E 0 ), gradient coefficient (γ)] and their associated variability, if data permit.                                                                                                                                                                                                                                                                                                                                                                                                                                                                                                                                                                                       |

### **3. STUDY DESIGN**

#### **3.1. Study Design Detail**

This will be an open label study where each Subject will participate in 2 study sessions (single and repeat dose). All Subjects will receive 160 mg EC micronised free-base darapladib as a single dose and as repeated daily dose for 28 days. There will be at least 4 days between dosing in the Single Dose Session and the first dose of the Repeat Dose Session due to the 96-hour PK sampling period following the single dose. PK samples will be collected over a 96-hour period after single dose in Session 1, and over a 24-hour period after Day 28 of repeat dosing, as well as over a 28-day duration following the last day of dosing of the repeat dose session. PD samples will be collected over a 24-hour period after Day 28 of repeat dosing, as well as over the 28-day duration following the last day of dosing of the repeat dose session.

Subjects will return approximately 28 days after the last dose of study medication for a follow-up visit. The total study duration for each Subject including the Screening, Treatment and Follow-up periods will be approximately 12 weeks.

#### **3.2. Discussion of Study Design**

##### **3.2.1. Design Rationale**

The study is designed to investigate the PK profiles of darapladib 160 mg after single dose and repeat dose in healthy Chinese Subjects. The study is open-label as the primary endpoint will not be influenced by Subjects knowing which medication they are receiving. The Subjects will have PK samples collected for more than 5 half-lives after dosing to enable a comprehensive PK profile to be generated. The design employed for this study is identical to the design of a previous Phase I study conducted on healthy western Subjects (Protocol Number LPL112498).

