##### **3.2.2. Dose Rationale**

As of December 2011, a total of approximately 652 healthy volunteers and 1179 patients from completed clinical trials had received darapladib. In overseas studies single and repeat oral QD doses of up to 100 mg of the non-EC freebase formulation and up to 480 mg of the EC free base micronised formulation of darapladib have been administered. Darapladib has been well tolerated. Mean half-life of darapladib was 126 hours following QD dosing of 160 mg EC tablets of micronised free-base darapladib to healthy western Subjects (Protocol Number LPL112498). Darapladib is expected to reach its steady state following repeat dosing of 28 days.

Study LPL110736, a double blind, randomized, parallel, placebo-controlled study, was conducted in Japan to investigate the safety, tolerability, PK and PD following 160 mg enteric coated, micronized free-base daily doses of darapladib in healthy Japanese male Subjects for 12 days. A substantial inter-ethnic difference in darapladib PK and PD was not observed.

Based on these data, this study will be conducted to determine the safety/tolerability, PK and PD of the EC, free base micronised darapladib 160 mg in the single dose session and repeat dose session in healthy Chinese Subjects. EC free base (micronised) darapladib 160 mg in this study is currently being evaluated in the ongoing global phase III studies of darapladib.

Darapladib will be administered as EC tablets formulated to begin disintegration at pH 5.5 and above. Under these conditions, the formation of 4-fluorobenzyl chloride, a potential alkylating agent that is an acid degradation product of darapladib that is formed only at very low pH in the presence of chloride ions, is anticipated to be negligible at this proposed dose.

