## PK/PD Sampling After Last Repeat Dose:

| Day:                          | 29 | 30 | 31 | 32 | 33 | 34 | 35 | 36 | 37 | 38 | 39 | 40 | 41 | 42 | 43 | 44 | 45 | 46 | 47 | 48 | 49 | 50 | 51 | 52 | 53 | 54 | 55 | 56 | Follow-up |
|-------------------------------|----|----|----|----|----|----|----|----|----|----|----|----|----|----|----|----|----|----|----|----|----|----|----|----|----|----|----|----|-----------|
| Outpatient visit              |    |    | X  | X  | X  | X  | X  |    |    | X  |    |    | X  |    |    | X  |    |    | X  |    |    | X  |    |    | X  |    |    | X  | X         |
| PK blood sample   | X  | X  | X  | X  | X  | X  | X  |    |    | X  |    |    | X  |    |    | X  |    |    | X  |    |    | X  |    |    | X  |    |    | X  |           |
| PD blood sample   | X  | X  | X  | X  | X  | X  | X  |    |    | X  |    |    | X  |    |    | X  |    |    | X  |    |    | X  |    |    | X  |    |    | X  |           |
| Discharge                     |    | X  |    |    |    |    |    |    |    |    |    |    |    |    |    |    |    |    |    |    |    |    |    |    |    |    |    |    |           |
| 12-lead ECG                   |    |    |    |    |    |    |    |    |    |    |    |    |    |    |    |    |    |    |    |    |    |    |    |    |    |    |    |    | X         |
| Vital signs                   |    |    |    |    |    |    |    |    |    |    |    |    |    |    |    |    |    |    |    |    |    |    |    |    |    |    |    |    | X         |
| Urine pregnancy test (women)  |    |    |    |    |    |    |    |    |    |    |    |    |    |    |    |    |    |    |    |    |    |    |    |    |    |    |    |    | X         |
| Hema/Chem/Urinalysis tests    |    |    |    |    |    |    |    |    |    |    |    |    |    |    |    |    |    |    |    |    |    |    |    |    |    |    |    |    | X         |
| AE review                     | X  |    |    |    |    |    |    |    |    |    |    |    |    |    |    |    |    |    |    |    |    |    |    |    |    |    |    |    | X         |
| Concomitant Medication Review | X  |    |    |    |    |    |    |    |    |    |    |    |    |    |    |    |    |    |    |    |    |    |    |    |    |    |    |    | X         |

1. After last day of repeat dosing PK and PD samples will be obtained at 36, 48, 72, 96, 120, 144, 168, 240, 312, 384, 456, 528, 600 and 672 hours post-dose

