## 8. DATA ANALYSIS AND STATISTICAL CONSIDERATIONS

### 8.1. Hypotheses and Treatment Comparisons

No formal hypothesis will be tested. An estimation approach will be taken and appropriate corresponding confidence intervals (CIs) will be used to address the comparisons of interest.

For the planned PK analysis, the PK parameters of darapladib (parent) and the pharmacologically active metabolite SB-553253 on Day 28 (**Repeat Dose Session**) will be compared to those on Day 1 (**Single Dose Session**) separately. The comparisons of interest will be expressed as the accumulation ratios ( $R_o$ ,  $R_p$ ,  $R_s$  and  $R_{cmax}$ ), as the data permit, according to the equations below:

$$\text{Observed Accumulation Ratio } (R_o) = \frac{\text{AUC}_{(0-\tau)} \text{ of Day 28}}{\text{AUC}_{(0-\tau)} \text{ of Day 1}}$$

$$\text{Predicted Accumulation Ratio } (R_p) = \frac{\text{AUC}_{(0-\infty)} \text{ of Day 1}}{\text{AUC}_{(0-\tau)} \text{ of Day 1}}$$

$$\text{Steady-State Accumulation Ratio } (R_s) = \frac{\text{AUC}_{(0-\tau)} \text{ of Day 28}}{\text{AUC}_{(0-\infty)} \text{ of Day 1}}$$

$$\text{Cmax Accumulation Ratio } (R_{cmax}) = \frac{C_{max} \text{ of Day 28}}{C_{max} \text{ of Day 1}}$$

For metabolite, AUC and  $C_{max}$  metabolite to parent ratio will be calculated on each day (Day 1 Single Dose Session and Days 28 Repeat Dose Session).

For the planned PD analysis, percent inhibition of plasma Lp-PLA2 activity will be calculated and summarized at each time point.

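### Single-dose sampling ends at 96 h, about 0.76 of the stated 126 h half-life, so Day 1 AUC(0-∞), a primary endpoint and the basis of Rp and Rs, rests on a large and possibly biased extrapolation with no reporting limit

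*Combined protocol and SAP*

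**What the plan says.** - Section 3.2.1 describes a study of profiles after single and repeat dosing and then states: "The Subjects will have PK samples collected for more than 5 half-lives after dosing to enable a comprehensive PK profile to be generated". It does not name the session.
- Section 3.2.2: "Mean half-life of darapladib was 126 hours following QD dosing of 160 mg EC tablets", in healthy western subjects. No other half-life is given.
- Section 3.1: "PK samples will be collected over a 96-hour period after single dose in Session 1", and "There will be at least 4 days between dosing in the Single Dose Session and the first dose of the Repeat Dose Session". The Time and Events tables (6.1) agree. The last single-dose PK sample is at 96 h. After the last repeat dose the schedule ends with "528, 600 and 672 hours post-dose".
- Section 2 lists as primary PK endpoints AUC(0-t), AUC(0-∞) ("area under the concentration-time curve from time zero (pre-dose) extrapolated to infinite time"), Cmax, Rcmax and Ro, under an objective that covers single and repeat dosing. Half-life is secondary. Rp and Rs are not in the endpoint table.
- Section 8.1: "The comparisons of interest will be expressed as the accumulation ratios", with Rp = Day 1 AUC(0-∞) / Day 1 AUC(0-τ) and Rs = Day 28 AUC(0-τ) / Day 1 AUC(0-∞).
- Section 8.3.2.3 plans non-compartmental analysis, half-life after both sessions, and 90% CIs for the ratios from a mixed model. These parameters are qualified only by whether the data allow them. No maximum extrapolated share, minimum span for the half-life fit or fitting window is stated.

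**The concern.** The coverage that 3.2.1 relies on exists after the last repeat dose but not after the single dose, and the single-dose session supplies Day 1 AUC(0-∞). That quantity is the observed area to 96 h plus C(96)/λz, with λz read from samples spanning less than one stated half-life. Two things can go wrong. If distribution is still contributing between 48 and 96 h, the fitted slope is too steep, the extrapolated area is too small, Rp reads low and Rs reads high. If decline is already mono-exponential, the slope is unbiased but poorly determined.

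At stake is interpretation. With linear kinetics and near steady state, Rs should be close to 1. A value above 1, or a longer half-life on Day 28 than on Day 1, could be taken as a change in kinetics with time when it reflects only a 96 h window set against a 672 h window. The planned CIs use residual variance and do not carry this error.

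**Working it through.** **Inputs from the documents.** Half-life 126 h (3.2.2); single-dose window 96 h (3.1, 6.1); last washout sample 672 h (6.1); 43 PK time points (6); 18 evaluable subjects and CVw 27.0% for AUC (8.2.1).

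**The plan's own statement.** Five half-lives = 5 × 126 = 630 h.
- After the last repeat dose: 672/126 = 5.33, so the statement reproduces.
- After the single dose: 96/126 = 0.76, so it does not.
- PK samples: 15 single-dose + 3 troughs + 11 on Day 28 + 14 afterwards = 43, the stated total. No later single-dose sample is planned.

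**Extrapolated share of Day 1 AUC(0-∞).** Let f be the terminal phase's share of total AUC. The documents do not give f, so it is an assumption. Ignoring absorption and any distribution left at 96 h, share beyond 96 h = f × 2^(−96/126) = 0.59 f.

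| f | Share extrapolated |
|---|---|
| 1.00 (mono-exponential) | 59% |
| 0.85 | 50% |
| 0.70 | 41% |
| 0.50 | 29% |
| 0.34 | 20% |

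A mono-exponential share of 20% or less would need a half-life of at most 96/log2(5) = 41 h.

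**Bias if decline is multi-phasic: one case by hand** (assumed distribution half-life 20 h, 80% of initial concentration in that phase, instantaneous input, no noise).
- C(t) = 0.8·2^(−t/20) + 0.2·2^(−t/126), so C(48) = 0.3052 and C(96) = 0.1467.
- With three equally spaced points (48, 72, 96 h) the log-linear slope is ln(0.3052/0.1467)/48 = 0.01527 per h. Apparent half-life = 0.693/0.01527 = 45 h, not 126 h.
- True AUC(0-∞) = 0.8 × 20/0.693 + 0.2 × 126/0.693 = 23.1 + 36.4 = 59.4, so f = 36.4/59.4 = 0.61.
- True area after 96 h = 23.1 × 0.036 + 36.4 × 0.590 = 22.3 (37%).
- Estimated AUC(0-∞) = (59.4 − 22.3) + 0.1467/0.01527 = 37.2 + 9.6 = 46.8, that is 46.8/59.4 = 0.79, or 21% low.
- With linear kinetics, Day 28 AUC(0-τ) equals single-dose AUC(0-672), so true Rs = 1 − 0.61 × 2^(−672/126) = 1 − 0.61 × 0.025 = 0.985. Estimated Rs = 0.985/0.787 = 1.25.

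**Same calculation over a grid** (assumed first-order absorption 0.4 per h, distribution half-life 6–24 h, f 0.30–0.90, fit at 48/72/96 h, no noise). AUC(0-∞) is about 3–23% low, apparent half-life is about 26–119 h, and Rs is about 1.01–1.28 against a true 0.98–0.99. The direction is the same in every case. A 20% extrapolation filter alone may miss this: with a 12 h distribution half-life and f = 0.6, the estimated share reads 18% when the true share is 36%.

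**If decline is mono-exponential.** The same fit returns 126 h and the correct AUC(0-∞). Only precision suffers: relative SE of λz = σ/(λz·√Sxx), with λz = 0.693/126 = 0.0055 per h and an assumed residual error of 10%.
- Fit at 24, 36, 48, 72, 96 h: Sxx = 3,341, relative SE = 0.1/(0.0055 × 57.8) = 31%; 5th–95th percentile of half-life about 83–263 h.
- Fit at 48, 72, 96 h: Sxx = 1,152, relative SE = 0.1/(0.0055 × 33.9) = 54%.

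**Set against the planned precision.** The stated 16.6% reproduces: exp(1.740 × √ln(1 + 0.27²) × √(2/18)) − 1 = 16.6%. If that width applied to Rs at the top of the grid, the lower 90% limit would be 1.28/1.166 = 1.10, which excludes 1 although the true value is about 0.98.

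**The case against.** The case for leaving the plan alone has several sound parts.

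- The 3.2.1 sentence names no session and is correct for the washout, while 3.1 states the 96 h window openly. This stands: the sentence needs limiting to one session and is not false throughout.
- A reader might infer that Day 1 AUC(0-∞) is mostly extrapolated. The documents do not support that. More than half requires f of about 0.85 or higher, and the protocol gives no phase split.
- The 59% share and the bias belong to different scenarios. Mono-exponential decline gives the largest share and no bias. The bias needs a distribution phase whose size is assumed here.
- The 126 h value comes from once-daily dosing in western subjects. Carrying it to a single dose in Chinese subjects is an assumption, though it is the only value available.
- Most primary PK endpoints are untouched. AUC(0-t) is observed and already primary, and Ro and Rcmax use only observed quantities. Half-life is secondary, and Rp and Rs have no primary status.
- The data-permitting qualifier lets the analyst withhold a parameter. That is a partial safeguard, but it gives no criterion.
- No hypothesis is tested, and steady state is judged from troughs. A false report of time-dependent kinetics is therefore a risk of misreading, not a planned conclusion.
- 3.2.1 says the design is identical to western study LPL112498, so any truncation bias might be shared. That would help a comparison between populations only if windows, method and disposition were the same. It would not make Day 1 AUC(0-∞), Rp or Rs correct within this study.

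**Conclusion.** The point holds in a limited form and should be settled before analysis. From the documents alone: single-dose sampling covers 0.76 of the stated half-life, the 3.2.1 coverage applies only after the last repeat dose, and a primary endpoint depends on the uncovered part with no stated limit on extrapolation. The single-dose half-life would be fitted over less than one half-life.

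The size depends on assumptions. Given 126 h, up to about 59% of Day 1 AUC(0-∞) is extrapolated, and more than 20% unless the terminal phase carries less than about a third of AUC. The 3–23% shortfall and the Rs of 1.01–1.28 hold for the assumed multi-phasic profiles and a 48/72/96 h fit. Under mono-exponential decline the problem is imprecision only.

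Two further inferences go too far: that the whole primary PK analysis is compromised, and that the trial will report time-dependent kinetics. Ro, Rcmax, Cmax and AUC(0-t) are unaffected, and nothing in the plan commits to reading Rs in that way.

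**What to change.** 1. In 3.2.1, limit the five-half-life statement to the washout after the last repeat dose.
2. In Section 2, keep the observed single-dose AUC(0-t), which is AUC(0-96) when the 96 h sample is quantifiable, with AUC(0-τ), Cmax, Ro and Rcmax as the primary PK measures. Move Day 1 AUC(0-∞) to secondary or exploratory and report its extrapolated fraction for each subject.
3. In 8.3.2.3, take terminal half-life from the 672 h washout and state that half-life is not compared between sessions.
4. In 8.1 and 8.3.2.3, label Rp and Rs exploratory, and state that Rs above 1 is not on its own evidence of time-dependent kinetics.

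A joint compartmental fit to all 43 samples per subject is an optional sensitivity analysis. It brings its own model dependence and should not replace the planned non-compartmental method.

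Cost: wording changes in the protocol and the reporting and analysis plan, with no new samples or visits. The downside is that Day 1 AUC(0-∞) loses primary status.
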